## 2. Background

At present malignant ovarian tumours are diagnosed at an advanced stage in 75 % of the cases and they result in the highest mortality figures of all gynaecological cancers. An estimated 22,430 new cases of ovarian cancer are expected to be diagnosed in 2007 in the United States, according to the American Cancer Society, with about 15,280 deaths. Worldwide there are more than 190,000 new cases of ovarian cancer each year, according to the International Agency for Research on Cancer. These figures underscore the need for effective tests to diagnose ovarian cancer at early stages and to improve management of patients with adnexal tumours.

The **IOTA study (International Ovarian Tumour Analysis)** is a multicentre collaborative project for the pre-operative characterisation of ovarian tumours based on predictive computer models.

The **first phase** of IOTA was conducted between 1999 and 2002. Several new mathematical models were developed based on the prospectively collected data of 1066 patients with a persisting adnexal tumour in 9 European Centres. Between 2002 and 2005 three centres continued the prospective collection in order to be able to perform an internal validation of mathematical models developed in IOTA phase 1. In this so-called IOTA **phase 1b** study a new dataset of 507 new patients was prospectively collected in 3 out of the 9 original IOTA centres. All models proved to perform excellent with area under the ROC curves of more than 0.94.

The **second phase** of IOTA consisted of an external validation of the models and this was conducted between 2005 and 2007. The diagnostic algorithms were prospectively validated on 2,093 patients with adnexal tumours in 19 centres in Belgium, Italy, UK, Sweden, Poland, Czech Republic, Canada, and China. A first analysis showed that overall performance of the logistic regression models was excellent (area under the ROC curve 0.94). A subgroup of “uncertain” tumours needs a reliable second stage test in order to help even experienced ultrasound examiners.

The **third phase** of the IOTA study is planned for 2009.

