### 3. Design

#### Number of patients / tumours

2,000 patients with at least one histologically examined adnexal mass will be recruited for the third part of the IOTA trial (i.e. the prospective testing of new mathematical models and second stage tests).

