#### **O6: Validation of a new model, based on grey scale ultrasound and colour Doppler information, specifically designed for “difficult” tumours**

Using subjective evaluation of grey scale and Doppler ultrasound findings, an experienced ultrasound examiner using a good ultrasound system can correctly classify ovarian tumours as benign or malignant in most cases. The experts reached in IOTA 1 and IOTA 1b a sensitivity of 88% (234/266) and 90% (129/143), respectively, and a specificity of 95% (762/800) and 93% (338/364) ([44], unpublished data). In 8% of the cases, the ultrasound examiner found it difficult to discriminate between benign and malignant tumours (90/1066 in IOTA 1, 39/507 in IOTA 1b) [45]. Borderline tumours were over-represented among these “uncertain” masses, being three times more common among the “uncertain” masses than among the other ones. Of those borderline tumours, 60% (33/55) were correctly classified (i.e., classified as malignant) by the expert, compared to 95% (762/800) of the benign tumours, 96% (162/169) of the primary invasive tumours and 93% (39/42) of the metastatic tumours [45]. A logistic regression model has been constructed using data of the 54 “uncertain” cases with papillary projections in IOTA 1, but its performance was not stable: the area under the ROC curve was 0.88 on the development set, but dropped to 0.73 on an independent test set. Combining all data available in IOTA 1, 1b and 2 (IOTA 2 data collection just recently closed), we now have full preoperative information of 3,500 tumours including 250 cases which were difficult to preoperatively predict according to the investigators. Moreover, tumours for which the output of the main logistic regression is close to the decision boundary can also be regarded as difficult to classify. Using all available grey scale ultrasound and colour Doppler data of difficult tumours in IOTA 1, 1b and 2, a logistic regression model has specifically been developed for these difficult masses, with an area under the ROC curve of 0.85 on both development and test set (unpublished data).

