### **Work package 1:**

**Objective 1: Prospective external validation of predictive mathematical models and pattern recognition to distinguish between malignant and benign adnexal masses**

The aim of this work package is to validate the IOTA mathematical models that predict the character of an adnexal mass in daily clinical practice using centre-specific cut-offs and to select those patients that are difficult to classify or to diagnose (i.e. with uncertain subjective assessment or uncertain predictive value) for a second stage examination. This work package is further subdivided in 6 tasks.

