### **Task 1.5: Patient selection for Second stage tests**

The IOTA 2 dataset enables us to describe the population characteristics of each centre in correlation with the performance of the models in that centre. This gives us the opportunity to define centre-specific cut-offs above which an adnexal mass is classified as malignant. Whenever the probability of malignancy is amongst the 15% that lies close to the decision boundary of LR1, the examiner will be obliged to perform one of the second stage tests. In this way, we expect that the adnexal masses of approximately 300 patients will be classified as “difficult” and will need a second stage test.

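### The protocol defines a difficult mass in three incompatible ways, and the expected count of about 300 follows from only one of them

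*Protocol*

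**What the plan says.** Three places in the protocol decide which masses count as difficult.

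- **Work package 1, aim.** Masses are to be selected "with uncertain subjective assessment or uncertain predictive value) for a second stage examination". Either source of uncertainty is enough.
- **Task 1.5.** The condition is "Whenever the probability of malignancy is amongst the 15% that lies close to the decision boundary of LR1", and in that case "the examiner will be obliged to perform one of the second stage tests". The subjective assessment is not mentioned. The task concludes that "we expect that the adnexal masses of approximately 300 patients will be classified as “difficult” and will need a second stage test".
- **Task 6.1.** Cases in which the clinician declares uncertainty are randomised 1:2 to standard procedure (arm A) or standard procedure plus the difficult-tumours model (arm B). LR1 is not mentioned. The expected total is again roughly 300, split 100 and 200.

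The target size in section 3 is that "2,000 patients with at least one histologically examined adnexal mass will be recruited". The Background describes the uncertain subgroup as one that "needs a reliable second stage test in order to help even experienced ultrasound examiners". The consortium's O6 section reports examiner difficulty in 8% of cases (90/1066 in IOTA 1, 39/507 in IOTA 1b) and counts about 3,500 earlier tumours, "including 250 cases which were difficult to preoperatively predict according to the investigators". It then names closeness to the model's boundary as a further source of difficulty, added to the first. Task 1.2 freezes the examiner's assessment and certainty grade before the model result is shown.

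**The concern.** Under the Work package 1 aim, a mass graded uncertain by the examiner but with an LR1 value far from the cut-off is selected for a second-stage examination. Under Task 1.5 it is not. For Task 6.1 it is eligible, and its LR1 value is irrelevant. Two centres could each follow the text and select different patients.

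Three things depend on the answer. The first is which population the second-stage results describe: masses that are hard for the examiner, hard for LR1, or either. The second is the expected numbers for Task 1.5 and Work package 6. The third is the set of historical comparisons in Tasks 2.2, 4.2 and 5.2, which draw controls from the difficult masses of IOTA 1, 1b and 2 without saying by which definition. Those controls are matched only on tumour type and age group. In Task 2.2 the outcome is the accuracy of the investigator's own diagnosis. If cases and controls are difficult for different reasons, part of any difference could come from the entry rule and not from the test.

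**Working it through.** **Inputs from the protocol**

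- Total: 2,000 patients (section 3), taken here as one mass per patient.
- LR1 band: 15% (Task 1.5).
- Examiner-uncertain rate (consortium section, O6): 90/1066 = 8.4%; 39/507 = 7.7%; combined 129/1,573 = 8.2%; stated as 8%. The pooled count is 250/3,500 = 7.1%.
- Randomisation 1:2 (Task 6.1).
- Overlap between examiner-uncertain masses and the LR1 band: not given, so it is varied from 0% to 100%.

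**1. The stated figure.** 0.15 × 2,000 = 300. The LR1 band alone reproduces Task 1.5 exactly, with nothing added for examiner uncertainty.

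**2. The same figure in Task 6.1.** Entry is by clinician uncertainty, so the examiner rate applies: 0.08 × 2,000 = 160. The other rates give 143 (7.1%), 154 (7.7%), 164 (8.2%) and 169 (8.4%). The literature section for O6 speaks of about 1 case in 10 that lacks a confident and correct diagnosis, which gives 200. None of these reaches 300, which needs a rate of 300/2,000 = 15%.

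Split 1:2, 160 gives 160/3 = 53 in arm A and 320/3 = 107 in arm B, against 100 and 200. That is 160/300 = 53% of the planned size.

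**3. The either/or rule.** At an examiner rate of 8%:

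- outside the band = 160 × (1 − overlap)
- selected in total = 300 + 160 × (1 − overlap)

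| Share of examiner-uncertain masses inside the band | Outside the band | Selected by either/or |
|---|---|---|
| 100% | 0 | 300 |
| 75% | 40 | 340 |
| 50% | 80 | 380 |
| 25% | 120 | 420 |
| 15% (independence) | 136 | 436 |
| 0% | 160 | 460 |

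With 7.1% or 8.4% in place of 8%, the upper limit becomes 443 or 469. The aim of Work package 1 and Task 1.5 agree only at complete overlap, which the protocol does not state.

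**4. Composition of the LR1 band.** Even at complete overlap, at most 160 of the 300 band masses (53%) are examiner-uncertain. At least 140 are there on the model's account only. So the results in difficult masses depend on the definition whatever the overlap.

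**5. What happens to the masses outside the band.** If every one enters Work package 6, one third (0 to 53) go to arm A with no model result. Two thirds (0 to 107) go to arm B and receive it. Nothing in Task 1.5 obliges contrast, proteomics, markers or 3D Doppler in either arm.

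**The case against.** A reader might infer that examiner-uncertain masses outside the LR1 band receive no second-stage test. The protocol does not support that. Task 6.1 admits clinician-uncertain cases whatever their LR1 value, and arm B receives the difficult-tumours model, which the Duration part of section 3 lists as a second-stage test. The close of the consortium's O6 section also lets investigators use the other four tests by preference. The Task 1.5 obligation is a minimum and does not close off other routes.

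A reader might also infer that the tests will be evaluated mainly in masses where the examiner is already confident. No figure for examiner confidence inside the band is given. In Tasks 2.2, 4.2 and 5.2 the cases are masses that had the test or marker, however they came to it. Nor is marker sampling shown to follow the LR1 rule: Task 4.1 refers to tumours needing a second-stage test without naming LR1, and the Summary describes blood sampling with no such limit.

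The overlap may be high. The IOTA phase 2 paragraph of the consortium section reports about 8% difficult masses for both expert and models, close to the decision boundary. That makes some overlap plausible but does not measure it, and O6 lists the two sources separately.

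One could argue that the 8% comes from experts and that phase 3 clinicians will be uncertain more often. However, the consortium section says that phase 3 uses the phase 2 centres, where experience varied. The rounded pooled counts leave about 250 − 129 = 121 uncertain among 3,500 − 1,573 = 1,927 later tumours, or 6.3%. That does not point towards 15%.

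Finally, the schematic of the algorithm is not shown and may state the entry rule. It could not remove a conflict between three passages of text. What stands of the objection limits the consequence; the inconsistency and the count in Task 6.1 remain.

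**Conclusion.** The point holds as an inconsistency of definition that carries into relied-on numbers. The aim of Work package 1, Task 1.5 and Task 6.1 select different masses. The figure of about 300 follows from the LR1 band and is carried over to an entry rule for which the protocol's own rate gives about 160 (143 to 169), that is about 53 and 107 per arm.

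Between 0 and about 160 examiner-uncertain masses fall outside the Task 1.5 obligation, and the either/or rule selects 300 to about 460. A narrower range would need an overlap figure that the protocol does not contain. These sizes assume that phase 3 has the earlier rate of examiner uncertainty, that the band captures 15% of 2,000, and that a clinician's statement of uncertainty in Task 6.1 means the same as the examiner's uncertain grade. The effect on masses outside the band could be nil if overlap is complete. The shortfall in Work package 6 does not depend on the overlap.

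**What to change.** - Reconcile the aim of Work package 1, Task 1.5 and Task 6.1 to one stated definition of a difficult mass. If Work package 6 is meant to differ, say so and why. Which trigger applies is for the sponsor to decide.
- Restate the expected numbers for Task 1.5 and for both arms of Work package 6 under that definition, with the overlap given as an explicit assumption. The sponsor may be able to estimate it from the IOTA 1, 1b and 2 data.
- Apply the same definition when drawing the historical controls of Tasks 2.2, 4.2 and 5.2.
- Report second-stage performance separately for masses that are examiner-uncertain only, in the LR1 band only, and both, using the certainty grade frozen before the model result.

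The cost is mainly protocol wording, since the certainty grade and the inputs to LR1 are already collected. The drawbacks are smaller subgroups, and an expected size for Work package 6 that may be less favourable than the one now stated.

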## **Work package 2:**

**Objective 2: Validation of intravenous ultrasound contrast agents: quantitative analysis of contrast uptake and washout in tumour**

The aim of this work package is to validate the preliminary study. Patients enrolled in task 2.1 will undergo a baseline (unenhanced) and contrast-enhanced examination. Correlations among results from B-mode, colour Doppler and CnTI-SonoVue examinations and the histopathologic diagnosis will be investigated. This work package is further subdivided in 2 tasks:

### **Task 2.1: Data collection**

To validate the existing model on its discriminating power new patients will be enrolled. Each patient will undergo an unenhanced (baseline) and a contrast-enhanced ultrasound evaluation. Ultrasound examinations will be performed with a high-resolution (9.0- to 5.0-MHz) Technos MPX endovaginal probe (Esaote SpA, Genoa, Italy). The contrast-enhanced examination will be performed with the CnTI technology applied to the transvaginal probe (Esaote SpA, Genoa, Italy) and with SonoVue (Bracco International BV, Amsterdam, the Netherlands). The CnTI technology works at very low acoustic pressure (derated pressure =126 kPa) or a very low mechanical index (<0.1). Each patient will receive SonoVue in a bolus dose of 4.8 ml. The examination starts from the injection of the bolus of SonoVue for 3 minutes or until the end of the contrast effect.

### **Task 2.2: Validation of the model**

The presence, the amount of vascularisation (colour score) and the pattern (regular or chaotic) of blood flow detected with colour Doppler and contrast-enhanced images will be investigated to assess whether the use of CnTI technology provides advantages with respect to the unenhanced ultrasound examination in the assessment of gynaecologic diseases, as seen in the preliminary results. Results will be validated using a case-control design. The above tumours for which intravenous contrast agents have been applied are considered as the “cases”. In IOTA 1, 1b and 2 a “historical control group” of difficult masses will be composed with two matching factors: 1) the same tumour type and 2) age (<50 versus ≥50). The difference in sensitivity and specificity of the investigator’s diagnosis between the cases with intravenous contrast and the control group will be assessed. The value of quantitative assessment of contrast ultrasound as second stage test in difficult tumours will also be compared with other second stage tests that were applied in the same patients.

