## **4. Detailed research description & Work Plan**

### **Introduction: IOTA Phase 3**

The work Plan is entirely focused to IOTA Phase 3 data collection and validation of the complete diagnostic algorithm. The aim of IOTA Phase 3 is to incorporate the IOTA mathematical models that predict the character of an adnexal mass in daily clinical practice using centre-specific cut-offs and to evaluate second stage tests in patients with adnexal masses that are difficult to classify in order to obtain more reliable results. For clarity of exposition we repeat here the objectives.

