### **The objective of IOTA Phase 3**

The main objective of this project is to improve preoperative diagnosis and subsequent management of patients with adnexal tumours by advanced algorithms in order to decrease morbidity and costs and in order to improve survival of patients with ovarian cancer. In particular, we aim to validate the added value of mathematical models as a new diagnostic tool in the prediction of ovarian cancer in clinical practice. First of all, we aim to prove their enhanced diagnostic performance and generalized applicability as a first stage examination. In cases where

prediction is unreliable, we aim to further improve the predictive performance of this diagnostic tool with second stage tests.

To achieve these objectives the project is divided in work packages each having its own sub-objective.

WP1: Prospective external validation of predictive mathematical models and pattern recognition to distinguish between malignant and benign adnexal masses

WP2: Validation of intravenous ultrasound contrast agents: quantitative analysis of contrast uptake and washout in tumor

WP3: Validation of proteomic analysis

WP4: Validation of a new set of tumour markers

WP5: Validation of 3D power Doppler

WP6: Validation of a new model, based on grey scale ultrasound and colour Doppler information, specifically designed for “difficult” tumours

The Work Plan now describes each of these Work Packages and details how each objective is achieved. The link between the different work packages is made clear in the schematic representation of the diagnostic algorithm. Realisation of the work plan should result in optimising all parameters of this diagnostic scheme with respect to diagnostic performance.

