#### **Task 4.1: Data collection**

In tumours needing a 2nd stage test in order to make a reliable preoperative diagnosis, a blood sample is taken and later on a combination of the following markers will be assessed:

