### Task 5.1: Data collection

In centres where a 3D ultrasound equipment is available, 3D power Doppler volumes of the adnexal mass will be collected. The vascularisation index will be calculated and the vascular tree described. This will be performed in the centre where the volumes are collected. Afterwards a copy of all of the stored 3D volumes will be sent to [name] (University Hospital, Malmö, Sweden) where she will independently recalculate all of the vascularisation indices. In this way, we will be able to correct for interobserver variability.

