### Task 5.2: Validation of the model

A case-control study will be performed to validate the use of 3D ultrasound as a second stage test. Masses in IOTA Phase 3 which have been investigated with 3D ultrasound are denoted as the “cases”. A historical control group is constructed using data of difficult masses available in IOTA Phase 1, 1b and 2. Two matching factors will be applied: 1) same tumour type and 2) age (<50 versus ≥50). This will enable us to assess whether 3D ultrasound results in a higher detection rate of malignant masses (higher sensitivity) or a decrease in the number of unnecessary exploratory laparotomies (higher specificity).

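### Tasks 2.2 and 5.2 define cases by receipt of contrast or 3D but controls by historical difficulty, and no single difficulty rule binds both sides

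*Protocol*

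**What the plan says.** **Cases.** Task 2.2: "The above tumours for which intravenous contrast agents have been applied are considered as the" cases. Task 2.1, which supplies them, says only "To validate the existing model on its discriminating power new patients will be enrolled". Task 5.2: "Masses in IOTA Phase 3 which have been investigated with 3D ultrasound are denoted as the" cases. Task 5.1 makes collection depend on equipment: "In centres where a 3D ultrasound equipment is available, 3D power Doppler volumes of the adnexal mass will be collected". None of the four carries a difficulty condition. Task 4.1 does: for tumours needing a second "stage test in order to make a reliable preoperative diagnosis, a blood sample is taken".

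**Controls.** Tasks 2.2, 4.2 and 5.2 all draw historical controls from difficult masses in IOTA 1, 1b and 2, matched on tumour type and on age below 50 or not. None says how a historical mass qualifies as difficult.

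**Phase 3 trigger.** Under Task 1.5, when the predicted probability is "amongst the 15% that lies close to the decision boundary of LR1, the examiner will be obliged" to carry out a second stage test. The aim of work package 1 adds masses whose subjective assessment or prediction is uncertain.

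**Intent.** The work plan's introduction sets out "to evaluate second stage tests in patients with adnexal masses that are difficult to classify". The objective section adds: "The link between the different work packages is made clear in the schematic representation of the diagnostic algorithm". That figure is not available in the text reviewed.

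**The concern.** Task 2.2 compares the sensitivity and specificity of the investigator's diagnosis between contrast cases and historical controls. Task 5.2 looks for higher sensitivity or specificity with 3D in the same way. Difficulty largely determines how often an examiner is right, yet it restricts only one side and is not a matching factor. If cases are easier on average than controls, a test that adds nothing can appear to help. If they are harder, a useful test can appear to fail. For 3D the historical comparison is the only one that Task 5.2 names, so nothing else in that task would expose the problem.

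**Working it through.** **1. The plan's own figure.** 0.15 × 2,000 = 300, which agrees with the roughly 300 difficult masses in Task 1.5. Task 6.1 also expects roughly 300, but randomises masses about which the clinician states uncertainty. At the historical examiner rates of 250/3,500 = 7.1% and 90/1,066 = 8.4% (O6, state of the art in the consortium), that criterion would give about 143 to 169 of 2,000. The same label therefore covers rules of different width.

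**2. The rules side by side.**

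| Group | Rule stated | Difficulty condition |
|---|---|---|
| Contrast cases (2.1, 2.2) | contrast was given | none |
| 3D cases (5.1, 5.2) | 3D was done, where equipment exists | none |
| Marker cases (4.1, 4.2) | second stage test needed, marker measured | yes |
| Phase 3 trigger (WP1 aim, 1.5) | 15% nearest the LR1 boundary, or uncertain assessment | obliges a test; does not exclude other masses |
| Historical controls (2.2, 4.2, 5.2) | difficult masses | yes, but undefined |

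For the historical data, O6 counts 250 of 3,500 masses as difficult by investigator judgement and says that nearness to the model boundary may also count. O1 (consortium section) gives about 8% for examiners and models alike. These are background figures; none is stated as the control rule.

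**3. Overlap, if the narrower label were used for controls.** With similar case mix, the share of a 15% band that could also meet a 7.1–8.4% definition is at most 7.1/15 = 48% to 8.4/15 = 56%.

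**4. Illustrative bias in specificity for a test with no effect.** From O6, pooled expert specificity in IOTA 1 and 1b is (762 + 338)/(800 + 364) = 94.5%, and the difficult share is (90 + 39)/(1,066 + 507) = 8.2%. Assumptions:

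- The same 8.2% applies among benign masses.
- Specificity in difficult masses, *s*, is not given; it is taken as 70%, 80% or 90%.
- A share *f* of cases is as difficult as the controls.
- The remaining cases are average easy masses (*k* = 1) or midway between difficult and easy (*k* = 0.5).

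Specificity in easy masses: *e* = (0.945 − 0.082*s*)/(1 − 0.082). Spurious difference: (1 − *f*) × *k* × (*e* − *s*).

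| *s* | *e* | *f* = 1 | *f* = 0.8, *k* = 1 | *f* = 0.8, *k* = 0.5 | *f* = 0.5, *k* = 1 | *f* = 0.5, *k* = 0.5 |
|---|---|---|---|---|---|---|
| 70% | 96.7% | 0 | 5.3 | 2.7 | 13.3 | 6.7 |
| 80% | 95.8% | 0 | 3.2 | 1.6 | 7.9 | 4.0 |
| 90% | 94.9% | 0 | 1.0 | 0.5 | 2.5 | 1.2 |

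Entries are percentage points. They depend strongly on *s*: at 55%, *e* is 98.0% and the *f* = 0.5, *k* = 1 entry becomes 0.5 × (98.0 − 55) = 21.5. The sign reverses if the controls are the wider group and the cases the harder one. For scale, Task 6.2 treats 10 points of specificity as clinically relevant, though for work package 6 only.

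**The case against.** The strongest reply is that the protocol, read as a whole, already confines these tests to difficult masses. The study objectives and rationale place second stage tests where prediction is unreliable. The duration section validates 3D for difficult tumours. The consortium's O5 text offers 3D as a second stage test, and work package 5 aims at difficult masses. Task 2.2 closes by speaking of contrast as a second stage test in difficult tumours, and Task 4.2 refers to work package 2 in those terms. The missing schematic may show the flow explicitly. This stands as evidence of intent, and it makes a large share of easy cases unlikely. It does not filter the analysed cases: both definitions rest on receipt of the test, Task 1.5 sets a minimum for testing rather than a limit, and Task 5.1 turns on equipment.

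A second reply is that operational selection of controls belongs in an analysis plan. The exact LR1 distance could be left there. But the protocol itself fixes the case definition, the control source, the matching factors and the comparison, and as fixed they are not aligned.

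Three further points stand:

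- **Direction is unknown.** O6 lets investigators choose tests by preference, and contrast needs written consent. They may use it on the hardest masses, which would bias against the test.
- **Matching on tumour type may absorb part of the gap.** Borderline tumours are over-represented among uncertain masses and were classified correctly in 60% (33/55), against 96% (162/169) of primary invasive tumours. Matching does not equalise difficulty within benign masses.
- **Work package 2 has comparisons in the same patients.** Baseline against contrast-enhanced scanning is free of this bias, and contrast is also compared with other second stage tests in the same patients.

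**Conclusion.** The point holds as a weakness in the definitions. In Tasks 2.2 and 5.2 difficulty is required of controls but not of cases, most clearly for 3D. On the intended reading too, nothing ties the Phase 3 trigger to the rule that selects historical controls, and this second part extends to Task 4.2. Any resulting imbalance biases the comparison of sensitivity and specificity.

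Direction and size cannot be fixed from the protocol. The bias is zero if both sides meet one rule. The illustration gives 0.5 to 5.3 points of specificity at 80% overlap and 1.2 to 13.3 at half, for an assumed 70–90% specificity in difficult masses and before any effect of matching. The 13.3 is an upper illustration, because masses near the LR1 boundary are unlikely to be average easy ones.

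A reader might infer more: that cases are unselected, that contrast and 3D are bound to look better than they are, or that the 7–8% historical label is the control rule and conflicts with the 15% band. The documents support none of these. The stated intent argues against unselected cases, no text shows that cases are easier, and the historical shares are never given as the control rule.

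**What to change.** State one pre-test difficulty rule and apply it to both sides.

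- **Rule.** Certainty category 3 in section 6, or an LR1 output within a stated distance of the cut-off. Use the centre-specific cut-off where one exists and one stated default elsewhere. Task 1.2 freezes the certainty rating before the model result; add that it also precedes contrast or 3D.
- **Cases.** Limit the analysed cases in Tasks 2.2 and 5.2 to masses that meet the rule. Report tested masses outside it separately. Cross-refer to Task 1.5 in Tasks 2.1 and 5.1.
- **Controls.** In Tasks 2.2, 4.2 and 5.2, select IOTA 1, 1b and 2 controls by the identical rule, distance and cut-offs.
- **Sensitivity analysis.** Repeat without IOTA 1 controls, because the IOTA logistic regression models were developed on those data.

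The cost is wording, a filter on recorded data, computing LR1 for the historical masses, and fewer analysed cases in work packages 2 and 5. Controls should not run short: a 15% band alone gives 0.15 × 3,500 = 525 candidates before matching. Without IOTA 1 it gives 0.15 × (507 + 1,938) = 367 or 0.15 × (507 + 2,093) = 390, depending on which of the protocol's two IOTA 2 totals is used. The change removes the difficulty imbalance only, not other differences between historical and current patients.
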